**Safety:**

Halo is an oral spray that is intended to provide reduce the microbial load in the oral cavity which may help protect against infections, including respiratory disease. The product has been formulated with a combination of lubricating/hydrating polymers and humectants. It contains 0.1% cetylpyridinium chloride as the active ingredient as well as the excipients, 35% glycerin copovidone, flavor, methylparaben, propylparaben, PEG-60 hydrogenated castor oil, sodium benzoate, sodium saccharin, water, xanthan gum and xylitol. Halo Spray is dosed from a conventional pump spray bottle without the aid of propellants. The consumer is directed to hold the spray bottle upright and to spray six times into the mouth without rinsing or spitting out. The recommended dosage is as required 3 times or 9 sprays per day.

**Toxicological Risk Analysis**

A safety assessment of this formulation was conducted with reference to BSEN ISO 10993, biological assessment of medical devices. This formulation was evaluated for acute oral toxicity, mucosal irritation, sensitization, subchronic toxicity, and genotoxicity potential. Evaluation of this formulation also took into consideration individuals with compromised immune systems as it is intended for use by individuals with medication-induced xerostomia as well as individuals with Sjogren's syndrome. Results of these evaluations indicate the product has an acceptable safety profile and poses no significant toxicological risk to individuals in these subpopulations under the intended conditions of use. The formulation consists of ingredients with a long history of safe use in oral healthcare products. With the exception of the flavor ingredients, Optamint 828653, Mouthwatering Liquid 15803210 and Optamint Optaflow225448, an adequate safety margin can be calculated to exist between the maximum daily exposure to each ingredient and exposures that can elicit adverse effects. All ingredients are of approved pharmaceutical grade (United States Pharmacopoeia and National Formulary, European Pharmacopoeia and British Pharmacopoeia) or comply with an internal standard. This formulation is composed of ingredients that are free of animal-origin and genetically modified-origin materials.

This formulation contains ingredients similar to other products intended to provide relief from the symptoms of dry mouth which have been shown to have acceptable safety profiles. There is no evidence to suggest additive or synergistic effects may arise following use of this product formulation.

The active ingredient, cetylpyridinium chloride has been used in mouth rinses in the United States since 1940. Cetylpyridinium chloride 0.025 percent to 0.1 percent has been marketed nationally in several products. Products containing cetylpyridinium chloride have also been marketed internationally. The more than 55-year U.S. marketing history is significant with respect to the ingredient's safety (Oral Health Care Drug Products for Over-the-Counter Human Use; Antigingivitis/ Antiplaque Drug Products; Establishment of a Monograph; Proposed Rules.(Federal Register, May 29,2003, Volume 68, Number 103: 32231-32287). Therefore, the risk of systemic toxicity following oral administration of cetylpyridinium chloride at the concentration used in this spray formulation is considered minimal.

Safety data on the flavor ingredients are available and are considered adequate to support their use in this formulation. The flavors used consist of mixtures of essential oils and other flavor ingredients, all of which are commonly used flavor constituents at levels similar to those used in current market products. Although actual safety margins cannot be calculated for these flavors, due to the proprietary nature of their composition, the suppliers evaluated the flavors for safety when used in this type of dosage form at the same concentrations at which they are used in this formulation and concluded that the flavors satisfy, according to the current state of knowledge, the safety requirements for the intended application under normal and reasonably foreseeable conditions of use. The flavor suppliers also declared that the flavors are acceptable for use in foods and cosmetics by their compliance with the provisions of Directives 88/388/EEC and 76/768/EEC and that the components of the flavors comply with an applicable regulation of FDA and/or are designated as being generally recognized as safe. As such these flavors are considered safe for inclusion in this formulation.

All of the remaining ingredients in this formulation are of very low toxicity and have a long history of safe use in oral healthcare products marketed in the United States and Europe. Their presence in this formulation, in the amounts specified, presents no significant toxicological risk.

This formulation contains trace amounts of the ICH Class 2 solvents methanol, 1,4-dioxane, ethylene glycol, toluene and pyridine as well as trace amounts of the ICH Class 3 solvents methyl ethyl ketone, ethyl acetate, ethanol, 2-propanol, acetone and 1-propanol. The residual concentrations of these solvents in this formulation are less than the concentration limits defined for each in the ICH guidance on residual solvents (CPMP/ICH/283/95) and the potential maximum daily exposure to each of these solvents from use of this formulation therefore conforms to the recommendations o f Option 1 o f the ICH guidance.

Assessment of potential hazard risks associated with use of Halo Spray reveals no significant safety issues. The formulation is similar to other products intended to provide relief from the symptoms of dry mouth which have been shown to have acceptable safety profiles. Proper use of this formulation as a mouth spray is not anticipated to be associated with any potential hazards. Although improper use of this formulation may be associated with potential hazards, the instructions and warning statements included in the product labeling are considered adequate to render the risk of such hazards acceptable. In summary, toxicological evaluation of Halo Spray concludes that the product does not present any significant toxicological risks to individuals when used as directed.

**Storage**

Halo is stable at room temperature. It can also be stored in the refrigerator (4^O^ C). At both storage temperatures, it was shown that the physical and microbiological are maintained. The Placebo should be stored in the refrigerator (4^O^ C). To maintain the blind both Halo and Placebo will be stored in the refrigerator (4^O^ C).

**Labeling:**

Halo is an OTC Drug (Antiseptic, Statement of Identity). It has an OTC Oral Healthcare Monograph active (cetylpyridinium chloride). It kills germs and may help guard against infections.

**Administration**

Based upon the preliminary studies that assessed the duration of the antimicrobial effects of Halo as reported in the preliminary studies and feasibility, subjects assigned to both study arms will be asked to spray the product intra-orally 3 times daily (Three sprays per use, total = 9 sprays per day). Although it is recognized that respiratory viruses most often and initially invade the nasopharynx (ref), it is still the case that the oropharynx is also involved in the pathogenesis of disease and there may be diffusion to the nasopharynx of orally administered product given the anatomic proximity of these anatomic sites.

As noted above, the study products will be supplied in 30 mL bottles to participants. Product should preferably be administered 30 minutes after any meal or brushing of teeth throughout the day and right before retiring. In between uses, the study product will be kept at room temperature. Subjects will be asked to retain bottles of all study products to be brought to scheduled visits to be counted by study personnel as a measurement of adherence. The date of initial use and the final use will be recorded on each study bottle.

**Clinical/Laboratory Evaluations and Study Schedule**

**Screening/Enrollment (See Appendix 2, Schedule of Events)**

Written informed consent will be obtained before any clinical evaluations are performed. The study will consist of 2 groups randomly assigned to Halo or matching placebo. The study visits will be conducted in the CWRU School of Medicine Room 3080. Screening and Enrollment will be performed at the same visit, a complete medical history and physical exam will be performed by study clinicians along with, serum chemistries, CBC with differential count, and a serum pregnancy test for women. Randomization into the study will be undertaken when it is determined that the subject has met all study inclusion criteria and has no exclusion criteria other than possible lab results. Since the screening and enrollment will be conducted at the same visit, subjects will begin the study prior to results of labs. If the labs result in an exclusion criteria the subject will be notified to discontinue and return unused study product. As noted in the safety section:. the study product has an acceptable safety profile and poses no significant toxicological risk to individuals. The formulation consists of ingredients with a long history of safe use in oral healthcare products.

A posterior pharyngeal and nasal swab will be obtained to ascertain baseline bacterial and fungal organisms and a multiplex PCR for respiratory viruses. Study product (after randomization) will be provided until the next scheduled visit, study procedures will be again reviewed, contact information for reaching study personnel will be provided, and study diaries will be distributed. Appointments for the 1^st^ monthly evaluation will be made.

**Scheduled Follow-up Visits**

At these visits, an interval medical and concomitant medication history will be obtained. Solicited and unsolicited adverse reactions will be ascertained. The study diaries will be reviewed with participants. An oropharyngeal exam will be conducted by study clinicians and a fuller symptom-directed physical exam will be performed if indicated. The intra-oral examination will be performed by utilizing the diagram provided in Appendix 3. A posterior pharyngeal and nasal swab will be obtained at each visit to ascertain bacterial and fungal organisms and a multiplex PCR for respiratory viruses. The enrollment and interim visit pharyngeal and nasal swabs will be analysed in real time, all other swabs will be stored for future use determined by funding. Study bottles will be collected and counted. Study product will be provided until the next scheduled visit, study procedures will be again reviewed, and contact information for reaching study personnel will be revisited. Appointments for the next monthly evaluation will be made.

**Final Study Visit**

This study visit will be conducted within 2 months after completing the last dose of Halo/Placebo. At this visit, an interval medical and concomitant medication history will be obtained. Solicited and unsolicited adverse reactions will be ascertained. An oropharyngeal exam will be conducted by study clinicians and a fuller symptom-directed physical exam will be performed if indicated. The intra-oral examination will be performed by utilizing the diagram provided in Appendix 3.

**Interim Visits**

Subjects will be instructed to contact study personnel in the event they develop an acute upper respiratory disease as defined above within 72 hours of onset of symptoms and signs (this allows for weekends and holidays). At these visits, an interval medical and concomitant medication history will be obtained. Solicited and unsolicited adverse reactions will be ascertained. An oropharyngeal exam will be conducted by study clinicians and a fuller symptom-directed physical exam will be performed if indicated. If pharyngitis with exudate is observed or suspected, a rapid group A streptococcal (GAS) screen will be performed. Subjects positive for Group A streptococcal infection will be given a prescription for appropriate antibiotics and a referral for follow-up care as needed. If individuals present with symptoms and signs of acute influenza fever, sore throat, myalgias, headache and chills, they will be tested for influenza and prescribed Tamiflu as needed. A posterior pharyngeal and nasal swab will be obtained to ascertain baseline bacterial and fungal organisms and a multiplex PCR for respiratory viruses. Any visit to a physician’s office, emergency department, urgent care center or the need for hospitalization will be recorded. Subjects will be carefully instructed to record the duration of each symptom and sign to be recorded in the study-supplied diaries.

**Statistical Analysis**

**Sample Size Calculations**

Initially, primary outcomes in the control group vs. the treatment group will be compared using the t-test for independent samples, and this technique was used to estimate sample sizes. Specifically, sample size calculations were carried out assuming that the two groups will be of equal size and that the random assignment will be balanced. Further, it was assumed that an average of 2 events would occur in the control group, contrasted against an average of 1.5 events in the treated group (SD = 1), and that the average duration of illness would be 4 days and 3 days in the control and treated groups, respectively (SD = 2). Taking alpha to be 0.05, a sample size of 23 per group would allow the detection of a 25% difference in primary outcomes between the two groups with 80% power. The sample size was increased to 51 per group to account for potential losses to follow-up.

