**Study Outcome Measures**

The **primary study objective** is to establish whether Halo will decrease the frequency, duration, and severity of acute respiratory disease and decrease the detection of respiratory viruses by multiplex PCR. After enrollment, subjects will be seen at scheduled monthly visits (+/- 7 days), 1-2 months after study completion and at interim visits when they develop a syndrome consistent with an acute upper respiratory disease. An acute upper respiratory disease will be defined as having fever to > 37.8°C and a non-productive cough and 2 or more of the following symptoms:

- Sore throat
- Rhinorrhea
- Sinus congestion
- Malaise

Patients will be provided with diaries (RedCap) to note any illness especially acute respiratory disease and to record the duration of each sign or symptom. Subjects will also be asked to take their temperature at 5p.m. each day and record their temperatures in the diaries. At interim visits related to the development of acute upper respiratory illness oropharyngeal swabs will be obtained for bacterial and fungal culture as well as respiratory virus multiplex PCR.

**Multiplex RT-PCR:** Following collection, an aliquot of the clinical sample will be placed in viral freezing media and stored at -80 degrees. Samples will be placed in 2ml glass collection tubes at a 1:1 ratio of clinical sample to viral freezing media. RNA from each clinical specimen will be extracted with the QiaAmp Viral RNA Mini Kit (Qiagen Inc., Valencia, CA) according to the manufacturer’s protocol. Extracted RNA will be stored at -80 degrees until processing.

Primers and probe sets for multiplex real-time RT-PCR detection of respiratory tract viruses have already been described [[35](#_ENREF_35)]. We will screen influenza positive samples under conditions as described with the exception that chlamydia and mycoplasma primer sets will be omitted. In addition, screening reactions for recently recognized viruses will be performed separately using real time primer sets as previously described [[36](#_ENREF_36), [37](#_ENREF_37)].

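### The 23 per group cannot be reproduced: the stated inputs need 64 (two-sided) or 51 (one-sided), so 51 per group leaves no allowance for losses

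*Protocol*

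**What the plan says.** The Sample Size Calculations section of the protocol gives almost every input. Primary outcomes are to be "compared using the t-test for independent samples, and this technique was used to estimate sample sizes". The allocation is 1:1, the calculation being made "assuming that the two groups will be of equal size and that the random assignment will be balanced". For the number of events it assumes a control mean of 2, "contrasted against an average of 1.5 events in the treated group (SD = 1"). For duration it assumes that "the average duration of illness would be 4 days and 3 days in the control and treated groups, respectively (SD = 2"). It then concludes: "Taking alpha to be 0.05, a sample size of 23 per group would allow the detection of a 25% difference in primary outcomes". The power claimed for this is 80%. The explanation of the enrolment target follows: "The sample size was increased to 51 per group to account for potential losses to follow-up".

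Two inputs are absent: whether the test is one-sided or two-sided, and the expected loss rate. The Protocol Schema words the hypothesis in one direction (fewer episodes) but does not name a one-sided test.

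**The concern.** A 25% difference is half a standard deviation on both outcomes. A two-group comparison of that size normally needs 50 to 65 per group, so 23 looks far too small. If 23 is wrong, the step from 23 to 51 is not a margin for drop-out, because part or all of it is needed to reach 80% power at all.

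Frequency and duration of illness are primary objectives, and the Statistical Analysis section plans to test both. A reader who trusts the paragraph will believe that the trial has 80% power with ample room for losses, and may read a null result as stronger evidence against a 25% reduction than it would be.

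**Working it through.** **Inputs, all from Sample Size Calculations.** Independent-samples t-test, 1:1 allocation, alpha 0.05, power 80%. Events: 2 against 1.5, SD 1. Duration: 4 against 3 days, SD 2.

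**Standardised difference.** Events: d = (2 − 1.5)/1 = 0.5. Duration: d = (4 − 3)/2 = 0.5. One calculation therefore serves both outcomes.

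**Attempt to reproduce 23.** The normal approximation is n per group = 2(z_alpha + z_power)²/d².
- Two-sided: 2(1.960 + 0.842)²/0.25 = 62.8, so 63. The exact noncentral-t result is 63.8, so **64**.
- One-sided: 2(1.645 + 0.842)²/0.25 = 49.5, so 50. The exact result is 50.2, so **51**.

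Other variants do not give 23 either. A one-sample or paired t-test needs 34 two-sided or 27 one-sided. Its one-sided normal approximation gives 25, the nearest figure, but that is the wrong design for two independent groups. Halving alpha for two outcomes gives 78. To obtain 23 two-sided, the SD for events would have to be about 0.59 rather than 1.

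**What 23 per group would deliver.** The noncentrality parameter is d·√(n/2) = 0.5 × √11.5 = 1.70, on 44 degrees of freedom. Power is 38% two-sided or 51% one-sided. The smallest d detectable with 80% power is 0.84 two-sided or 0.74 one-sided. In events that is 0.84/2 = 42% or 0.74/2 = 37%, against the claimed 25%.

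**What 51 per group delivers.** The noncentrality parameter is 0.5 × √25.5 = 2.52, on 100 degrees of freedom. The loss rates in the table are my assumptions, since the protocol gives none.

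| Loss (assumed) | Analysed per group | Power, two-sided | Power, one-sided |
|---|---|---|---|
| 0% | 51 | 71% | 81% |
| 10% | 46 | 66% | 77% |
| 20% | 41 | 61% | 73% |

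**Allowance for loss.** Taken at face value, moving from 23 to 51 corresponds to a loss of 1 − 23/51 = 55%. But the complete-data requirement is 51 (one-sided) or 64 (two-sided), so the reserve is 51 − 51 = 0, or 51 − 64 = −13 per group.

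**Precision at 51 per group.** The 95% confidence interval half-width for the difference in mean events, with SD 1 and complete data, is 1.984 × √(2/51) = 0.39 events.

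**The case against.** The strongest objection concerns sidedness. One might say flatly that the design needs 64 per group and has only 71% power. The protocol does not support that without a condition: it gives alpha as 0.05 and stops there. Two-sided is the usual reading, but the directional hypothesis leaves a one-sided test open. On that reading 51 per group reaches 80.6% with complete data, and the design lacks only the reserve for losses. This objection stands, and both sets of figures have to be carried.

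Three further inferences are tempting and go too far.

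- That 51 equals the one-sided requirement suggests where it came from, but the protocol shows no derivation, so its origin is not proved. Nor does the protocol say that the team considers a 55% loss tolerable; it states no rate.
- SD = 1 is below the Poisson value for means of 2 and 1.5 (√2 = 1.41 and √1.5 = 1.22). A reader might call that a second error. It is a stated planning assumption; a count with variance below its mean is unusual but possible, and the count regression in the Statistical Analysis section is a supplement with no named distribution.
- The illness definition is demanding ("fever to > 37.8°C and a non-productive cough and 2 or more of the following symptoms"), and one might infer that 2 events in 75 days is too many. The protocol gives no event rate by which to judge this.

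It is also fair to say that this is a pilot, and that the Statistical Analysis section already promises confidence intervals. That limits the harm from a wrong power statement but does not make the statement correct.

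**Conclusion.** The sample-size paragraph is wrong as written. Two conclusions hold whichever sidedness applies: 23 per group does not give 80% power for a 25% difference (it gives 38% or 51%), and 51 per group contains no allowance for losses, because it is at or below the number needed with complete data. The power actually available at 51 per group depends on the undeclared sidedness. If any participants are lost, it falls below 80% two-sided, and one-sided it does so with a loss of even one per group (79.9% at 50).

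These results rest only on the protocol's own means, SDs, test and alpha. The 10% and 20% losses are illustrative. The SD matters as a sensitivity point only: if the variance equalled the mean in each group (an assumption), d would be 0.5/√1.75 = 0.38, and power at 51 per group would be about 47% two-sided or 60% one-sided.

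**What to change.** Keep 102 participants and rewrite the paragraph, in this order:

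1. Declare whether the t-test is one-sided or two-sided.
2. Delete the claim that 23 per group suffices, and the statement that 51 accounts for losses.
3. State the power that 51 per group gives under the declared sidedness with complete data (71% two-sided or 81% one-sided), and again at a stated assumed loss rate (for example 61% or 73% at 20%).
4. As this is a pilot, add the expected precision: a 95% confidence interval half-width of about 0.39 events at SD 1.
5. Optionally, add one sentence showing how power changes if the variance of the event count equals its mean. SD = 1 need not be replaced.

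The change is to wording only and needs no further participants. The cost is that the stated power becomes less favourable.

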**Protocol Schema**

A Pilot Study of the Safety, Tolerability, and Effectiveness of Halo to Prevent Acute Upper Respiratory Illness and Respiratory Virus Infections

**DESIGN** This is a randomized, double-blinded, placebo-controlled clinical trial

**DURATION** Participants will be on treatment for 75 days. A follow up visit will occur within 2 months after treatment ends.

**SAMPLE SIZE** 51 participants each in the treatment and placebo arms

**POPULATION** Healthy men and women 18 to 45 years old, inclusive

**INTERVENTION** Participants will be randomized with equal proportion (51 each) into one of the following 2 groups:

- Halo administered intra-orally by spray Three times daily
- Placebo administered intra-orally by spray Three times daily

**HYPOTHESIS** The use of Halo sprayed intra-orally three times daily

will be associated with fewer episodes and duration of acute

respiratory diseases and less frequent detection of important

respiratory viruses confirmed by multiplex PCR

**PRIMARY OBJECTIVES** 1. To establish whether Halo will decrease the

frequency of acute upper respiratory illness

2. To assess whether Halo will decrease the duration

and severity of acute upper respiratory illness

**SECONDARY**  1. To assess the tolerability, acceptability and adherence to

**OBJECTIVES** Halo

2. To compare whether acute upper respiratory disease in

those receiving Halo compared to placebo is associated with differences in absenteeism (from work or school) and visits to physicians’ offices, emergency departments and urgent care centers

3. To determine whether Halo will decrease

the detection of respiratory viruses by PCR

4. To evaluate the effect of Halo on bacterial and fungal

microflora in the oropharynx

5. To evaluate the effect of Halo on those who did and did not receive the influenza vaccine.

**ENDPOINTS** 1. Frequency and duration of clinical respiratory disease at

interim visits and assisted by patient diaries

2. Intra-and extra-oral exams

3. Solicited and unsolicited adverse events

4. Respiratory virus multiplex PCR

5. Bacterial (oral streptococci, Group A streptococcus) and

fungal cultures

6. Bottle counts and self-report for adherence

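### On the protocol's own inputs, 23 per group gives 38% power (two-sided), not 80%, and 51 per group gives 71% before any losses, so 51 contains no allowance for dropout

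*Protocol*

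**What the plan says.** Under Statistical Analysis, the Sample Size Calculations section states that the primary outcomes will be "compared using the t-test for independent samples, and this technique was used to estimate sample sizes". It assumes equal groups and gives two scenarios:

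- number of events: mean 2 in controls, 1.5 on treatment, SD 1;
- duration of illness: mean 4 days in controls, 3 days on treatment, SD 2.

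The significance level is given as "Taking alpha to be 0.05", without saying one- or two-sided. The result is stated as follows: "sample size of 23 per group would allow the detection of a 25% difference in primary outcomes between the two groups with 80% power". It is followed by the explanation of the enrolled number: "The sample size was increased to 51 per group to account for potential losses to follow-up". No loss rate is given. The Protocol Schema carries the same enrolment figure, "51 participants each in the treatment and placebo arms".

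**The concern.** A difference of half a standard deviation is a moderate effect, and 23 per group is far too few to detect it with 80% power in a two-sample t-test. The step from 23 to 51 is also implausible as a loss allowance: it would mean planning to lose 1 − 23/51 = 55% of participants over 75 days of treatment.

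As written, the reader believes that the trial has 80% power with more than half of its sample in reserve. Two things follow. A non-significant result may be taken as evidence against a 25% reduction that the trial had a substantial chance of missing. And the team may tolerate attrition that the design cannot absorb. Some attrition is foreseeable: under Screening/Enrollment, "subjects will begin the study prior to results of labs", and those whose results turn out to be exclusionary are told to stop.

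**Working it through.** **Inputs**, all from Sample Size Calculations: independent-samples t-test, 1:1 allocation, alpha 0.05, target power 80%, and the means and SDs listed above. These are taken as given; only the arithmetic is checked.

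**Standardised difference**, d = (difference in means)/SD:

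- events: (2 − 1.5)/1 = 0.5
- duration: (4 − 3)/2 = 0.5

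Both are 25% of the control mean (0.5/2 and 1/4), so one calculation serves both outcomes.

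**Attempt to reproduce 23 per group.** The normal approximation is n per group = 2(z for alpha + z for power)²/d².

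- Two-sided: 2(1.960 + 0.842)²/0.25 = 62.8. The exact noncentral-t calculation gives 63.8, so **64**.
- One-sided: 2(1.645 + 0.842)²/0.25 = 49.5. The exact calculation gives 50.2, so **51**.

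Other readings were tried at 80% power and alpha 0.05 unless noted:

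| Reading | n required |
|---|---|
| Paired or one-sample t-test, two-sided / one-sided | 34 / 27 |
| Duration SD of 2 read as a variance, two-sided / one-sided | 33 / 26 |
| Two primary outcomes, alpha 0.025 each, two-sided | 78 |
| Poisson counts, means 2 and 1.5, two-sided | about 110 |

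None gives 23. To arrive at 23 with a two-sided test, the SD of the event count would have to be about 0.5/0.845 = 0.59 rather than 1.

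**Power at d = 0.5** (exact noncentral t). The protocol states no loss rate, so the 10% and 20% rows are assumptions.

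| Analysed per group | Two-sided 0.05 | One-sided 0.05 |
|---|---|---|
| 23 | 38.2% | 51.0% |
| 41 (51 less 20%) | 60.9% | 72.6% |
| 46 (51 less 10%) | 66.0% | 76.9% |
| 51 (no loss) | 70.6% | 80.6% |
| 64 | 80.1% | 87.9% |

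**Difference detectable with 80% power, two-sided.** As a percentage of the control mean this is d × 1/2 for events and d × 2/4 for duration, so d/2 in both cases.

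| Analysed per group | d | Events | Days | % of control mean |
|---|---|---|---|---|
| 23 | 0.845 | 0.84 | 1.7 | 42% |
| 41 | 0.626 | 0.63 | 1.3 | 31% |
| 46 | 0.590 | 0.59 | 1.2 | 30% |
| 51 | 0.560 | 0.56 | 1.1 | 28% |

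**What 51 is.** It equals the uninflated one-sided requirement (50.2, rounded up). Whether it was derived that way cannot be known from the protocol, but it cannot also contain a margin for losses: even one-sided, a 10% loss takes power below 80%. A two-sided design keeping 80% power would need 64/0.9, rounded up to 72 per group at 10% loss, or 64/0.8 = 80 per group at 20% loss.

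**The case against.** The strongest objection is sidedness. The protocol does not state it, and the hypothesis in the Schema is directional: Halo "will be associated with fewer episodes and duration of acute" respiratory disease. On a one-sided test, 51 per group gives 80.6% power, the enrolled sample reaches its target if nobody is lost, and the chance of missing the planned effect is 19% rather than 29%. This stands to the extent that the 38% and 71% depend on the two-sided reading and must be labelled so. It does not rescue the paragraph: 23 per group gives only 51% one-sided, and 51 is then the bare requirement with nothing spare. Two-sided is also the ordinary reading of an unqualified alpha of 0.05 for a t-test.

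A second objection is that this is a pilot, that estimation is an additional focus, and that confidence intervals are promised, so a reader can see whether a 25% effect is excluded. That softens the consequence, and it is why no extra enrolment is asked for. But the protocol makes a formal power claim, names efficacy on frequency and duration among its primary objectives, and plans t-tests on both. A pilot need not be powered; a power figure that it states must still be right.

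Third, participants stopped for screening laboratory results are not said to be dropped from the analysis, and the protocol encourages follow-up after withdrawal. That is fair: how far they reduce the analysed number is unknown. The finding does not depend on them.

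**Conclusion.** The concern holds. On the protocol's stated means, SDs, test and alpha, 23 per group does not give 80% power (38% two-sided, 51% one-sided), and 51 per group includes no allowance for losses (71% two-sided, 81% one-sided, with none lost). On the two-sided reading, the chance of missing the planned 25% effect is 29% with no losses, 34% at 10% loss and 39% at 20% loss; one-sided it is 19%, 23% and 27%. The loss rates are assumptions.

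These powers are conditional on the section's inputs, including its treatment of duration as available for every participant. If only those who fall ill contribute a duration, power for that outcome is lower. The paragraph must be corrected, because it is the only quantitative justification of the trial's size and it errs in the favourable direction.

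**What to change.** In Sample Size Calculations, delete the figure of 23 per group and the sentence saying that 51 covers losses to follow-up. State that the test is two-sided, and replace the deleted text with wording such as:

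> Under the means and SDs above, 51 per group gives 71% power (t-test, two-sided alpha 0.05) for a 25% (0.5 SD) difference with no losses, 66% at 10% loss and 61% at 20% loss. The difference detectable with 80% power is 28% with no losses and 30–31% with 10–20% loss. A non-significant result does not exclude a 25% effect.

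If the sponsor did intend a one-sided test, the protocol must say so and quote the matching figures (81%, 77% and 73%), still without claiming a loss allowance.

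The cost is one paragraph of wording and a less favourable stated power. Enrolment and design do not change.
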